## Materials and methods

### Study setting

This pilot study is a single-center, open-label, randomized controlled trial with a target sample size of 24 participants. Figure 1 shows a summary of the trial. The main eligibility criterion is meeting the diagnostic criteria for CKD. After a 2-week run-in period, participants will be allocated 1:1 to the intervention and control groups. During the intervention period, the intervention group will receive standard CKD dietary therapy with an additional intake of 50 g of sake lees per day for 8 weeks, whereas the control group will only receive the standard CKD dietary therapy. After the intervention, both groups will be observed for a period of 4 weeks. The primary endpoint is the change in serum indoxyl sulfate. The secondary endpoints are the changes in the serum p-cresyl sulfate and plasma D-alanine levels as well as fecal microbiome. The measurements for the endpoints will be performed at baseline and at 8 and 12 weeks.

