### Sample size

The sample sizes for the intervention and control groups will be 12 cases each. The number of cases is set based on feasibility and the recommended number of cases for the pilot study [14]. The maximum sample size allowed for entry will be 30 in total for both groups, considering the possibility of discontinuations.

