### Recruitment, run-in, and randomization

Recruitment will be conducted at the Department of Nephrology and Rheumatology, Kanazawa University Hospital (Kanazawa City, Ishikawa, Japan). The patients who met the eligibility criteria will be given a 2-week run-in period to eliminate the influence of food or drugs on the intestinal environment. During the run-in period, the intake of sake lees is prohibited. The participants are prohibited from consuming functional foods or drugs labeled to improve the intestinal environment. The consumption of yogurt or other common fermented foods is acceptable. A dynamic allocation strategy using the minimization method will be used for randomization. The allocation ratio is set at 1:1, with allocation adjustments for age (<75 or ≥75 years) and eGFR (15 to <30 or 30 to <60 mL/min/1.73 m^2^). Subjects will be automatically randomized using a web-based case registration and randomization system.

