### Statistical analysis

The primary and secondary endpoints will be tested using unpaired *t* tests for the measurement changes from baseline to week 8 between the intervention and control groups. As a secondary analysis, the changes between the intervention and control groups at baseline, 8 and 12 weeks will be tested using repeated measures analysis of variance. A multivariable regression analysis will be performed on the change in serum indoxyl sulfate levels from baseline to week 8, using age, sex, and eGFR at baseline as covariates. A two-tailed significance level of *p* < 0.05 will be used.

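### The only planned analysis of the week-12 data is a three-visit repeated-measures ANOVA that cannot separate the on-treatment effect from its persistence after stopping (minor, cheap to improve)

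*Protocol article*

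**What the plan says.** The Statistical analysis section of the Protocol article sets out three analyses.

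- **Main comparison.** Unpaired t "tests for the measurement changes from baseline to week 8 between the intervention and control groups", for the primary and secondary endpoints.
- **Secondary analysis.** Here "the changes between the intervention and control groups at baseline, 8 and 12 weeks will be tested using repeated measures analysis of variance".
- **Regression.** A multivariable model for the week-8 change in serum indoxyl sulfate, with age, sex and baseline eGFR as covariates.

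The first and third stop at week 8, so the ANOVA is the only described use of the week-12 measurements. Table 2 nevertheless schedules week 12 for every outcome except the food frequency questionnaire (FFQg).

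Study setting explains what week 12 is: the intervention lasts 8 weeks, and "After the intervention, both groups will be observed for a period of 4 weeks". On numbers, the Sample size section says "The sample sizes for the intervention and control groups will be 12 cases each" and "The maximum sample size allowed for entry will be 30 in total for both groups, considering the possibility of discontinuations".

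**The concern.** The three visits differ in kind. No treatment effect can exist at baseline, and a change from baseline measured at baseline is zero by construction. Week 8 is the end of treatment. Week 12 is after withdrawal. A repeated-measures ANOVA takes them as three levels of one time factor and returns omnibus tests. The article does not say which term is to be read.

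The design implies two questions: is there an effect on treatment, and does it last after stopping? The t test and the regression cover the first. Only this ANOVA could address the second, and neither of its between-group tests isolates it.

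The Discussion and Conclusion say that the pilot will inform the design of a later randomised trial. For that, an estimate with an interval at each visit is worth more than one p-value over all three.

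**Working it through.** **Inputs from the article:** 12 per arm, 1:1 allocation, two-sided 5% level, visits at baseline, week 8 and week 12. There is no planned power, effect size or SD to reproduce, because "The number of cases is set based on feasibility and the recommended number of cases for the pilot study".

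**Assumptions:** SD of 1 at each visit, equal correlation r between visits (0.6 or 0.8), and group differences at the three visits of 0, d and cd. Here d = 0.8 SD, and c is the fraction of the effect left at week 12 (0, 0.5 or 1). Equal correlation satisfies sphericity, which is the favourable case for the ANOVA.

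**1. Week-8 t test on change**

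SE = √[(2/12) × 2(1 − r)] = 0.365 (r = 0.6) or 0.258 (r = 0.8).
Noncentrality = 0.8/SE = 2.19 or 3.10 on 22 df, so power is 55% or 84%. It does not depend on c.

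**2. ANOVA group main effect**

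This compares each patient's mean over the three visits. The expected difference is d(1 + c)/3 = 0.267, 0.400 or 0.533 for c = 0, 0.5 or 1.
SE = √[(2/12)(1 + 2r)/3] = 0.350 (r = 0.6) or 0.380 (r = 0.8).
For example, with c = 0 and r = 0.6 the noncentrality is 0.267/0.350 = 0.76 and power is 11%.

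**3. ANOVA group-by-time interaction**

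This is an F test on 2 and 44 df with noncentrality (12/2) × S/(1 − r), where S is the sum of squared deviations of (0, d, cd) from their mean.

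- c = 0: S = d² − d²/3 = 0.667d²
- c = 1: S = 2d² − (2d)²/3 = 0.667d²
- c = 0.5: S = 1.25d² − (1.5d)²/3 = 0.5d²

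With d² = 0.64, the noncentrality is 6.4 (c = 0 or 1) and 4.8 (c = 0.5) at r = 0.6. At r = 0.8 it is 12.8 and 9.6.

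**Power by effect remaining at week 12**

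| Test | r | none | half | all |
|---|---|---|---|---|
| Week-8 t test | 0.6 | 55% | 55% | 55% |
| | 0.8 | 84% | 84% | 84% |
| Group main effect | 0.6 | 11% | 19% | 31% |
| | 0.8 | 10% | 17% | 27% |
| Interaction | 0.6 | 58% | 46% | 58% |
| | 0.8 | 88% | 77% | 88% |

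For the interaction, S is the same at c = 0 and c = 1. Complete loss of the effect and complete persistence therefore give exactly the same distribution of the test statistic. The test cannot distinguish them at any sample size under these assumptions.

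**Sensitivity.** With d = 1.0 and r = 0.7 the pattern is the same (none/half/all):

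- t test: 86% throughout
- main effect: 14/26/41%
- interaction: 90/79/89% by simulation

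In simulation with no effect, all three tests have a type I error of about 5%.

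**Precision of separate contrasts.** On simple change scores, the week-8 and week-12 contrasts each have the SE in step 1. The 95% half-width is 2.074 × 0.365 = 0.76 SD, or 2.074 × 0.258 = 0.54 SD. At this size the persistence estimate will be rough, but its uncertainty will be visible.

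**Complete cases.** Going from 12 to 10 complete patients per arm (d = 1.0, r = 0.7, c = 0) lowers interaction power from 90% to 83%.

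**The case against.** The strongest defence is that this is a labelled secondary analysis in a 24-patient pilot sized on feasibility. Comparing changes between groups over time naturally means the interaction, and that test is not weak: it slightly beats the t test in four of the six scenarios. The week-8 question already has its own test and regression. Naming the term, the contrasts and the missing-data handling is ordinary SAP content that a condensed article may leave out.

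Much of this stands, and three stronger readings that a reader might infer are not supported.

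- **The ANOVA dilutes the effect in general.** It does so for the main effect. The interaction loses power only under partial persistence.
- **The ANOVA answers no stated question.** The 4-week follow-up with week-12 measurements implies a time-course question. A result that differs from the week-8 test because the effect has washed out is not a contradiction.
- **Up to 20% of patients are lost.** Six of 30 is the room between the entry cap and the target of 24. The article does not say when those patients would leave. Anyone gone before week 8 is lost to the t test as well and adds no outcome to a mixed model. Only patients seen at week 8 and missing at week 12 are lost specifically here, and their number is not given.

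The defence does not remove the main point. The article has chosen the method and the visits, so this is more than an omitted detail. Reading the interaction rather than the main effect still leaves a 2-df test that cannot tell a lost effect from a lasting one.

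**Conclusion.** The point holds as a minor weakness in a secondary analysis. The primary week-8 comparison is untouched, and no error-rate problem follows.

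What the ANOVA cannot do is say what happened at week 12, although it is the only described analysis of those data. Its cost depends on the term read. The main effect has about 10–31% power where the week-8 t test has 55–84%. The interaction has similar power to the t test (58–88%) if the effect vanishes or fully persists, and 46–77% if half remains.

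The power figures rest on an assumed 0.8 SD effect, correlation of 0.6 to 0.8, equal correlation between visits and 12 complete patients per arm. The article supplies only the arm size and the significance level. The equality of interaction power under loss and full persistence does not depend on the size of the effect or on the value of the correlation, but it does use equal correlation between visits.

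**What to change.** Replace the repeated-measures ANOVA with a mixed model for repeated measures:

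- **Outcomes:** the week-8 and week-12 values.
- **Covariates:** the baseline value of the endpoint and the minimisation factors, age and eGFR.
- **Fixed effects:** group, visit and group-by-visit, with an unstructured covariance over the two visits and a small-sample df method such as Kenward-Roger.
- **Pre-specified contrasts, each with a 95% confidence interval:** the group difference at week 8 (on treatment) and at week 12 (after stopping).
- **Scope:** only endpoints measured at baseline, week 8 and week 12. The FFQg has no week-12 measurement and should be excluded.

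This uses the same data and keeps a patient who has week 8 but not week 12. The cost is revised analysis wording, slightly more analysis work and a few degrees of freedom for the covariates. Visits, sample size and the primary test stay as they are.

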## Discussion

This pilot study involving CKD patients will evaluate the changes in blood uremic toxin levels during standard CKD dietary therapy with sake lees intake. The intervention group will receive 50 g per day of sake lees for 8 weeks in addition to the standard CKD dietary therapy, and the changes in serum indoxyl sulfate levels will be compared with that of the control group.

Spherical carbon adsorbents have been used as a therapeutic agent to target uremic toxins in the intestine of CKD patients. In a large clinical trial in CKD patients [carbonaceous oral adsorbent’s effectiveness on progression of chronic kidney disease (CAP-KD study)], patients receiving spherical carbon adsorbents had a significantly slower decrease in eGFR [18]. Similarly, in the multinational, randomized, double-blind, placebo-controlled evaluating prevention of progression in CKD (EPPIC) and the carbonaceous oral adsorbent’s effectiveness on progression of chronic kidney disease (KAP-KD) trials, the decrease in eGFR was significantly slower in patients receiving spherical charcoal [19, 20]. However, the adherence to the oral administration of spherical carbon adsorbents was poor due to the high treatment doses and oral discomfort. Constipation as a side effect also contributes to poor adherence.

A common dietary therapy for dysbiosis includes intake of probiotics such as yogurt and prebiotics such as fruits and vegetables. However, CKD patients may have difficulty actively consuming yogurt due to phosphorus restriction and fruits or vegetables due to potassium restriction. Dietary supplements have also been tested as probiotics and prebiotics for CKD patients. For example, probiotics and prebiotics have been reported to reduce the p-cresyl sulfate levels in CKD patients [21]. These supplements are also difficult to obtain and relatively expensive; hence, making a generalization may be difficult.

Sake lees is affordable and easily available in Japan. Sake lees contains dietary fiber and many of bacteria types. It is also low in phosphorus and potassium and contains no salt, making it suitable for CKD patients. As one of its effects, a study on people with constipation reported that consumption of a drink containing sake lees for 4 weeks changed the occupancy rate of intestinal bacteria [22]. Constipation also improved when 50 g of sake lees was consumed for 3 weeks [7].

In addition to the bacteria and dietary fiber, sake lees contains D-alanine and D-serine, which may potentially have renoprotective effects [8, 9]. We have also confirmed that D-alanine is produced by bacteria present in the body [23]. Therefore, consumption of sake lees may exert a renoprotective effect due to the D-amino acids and D-amino acid-producing bacteria present in sake lees.

Based on these findings, the intake of sake lees in CKD patients has a renoprotective effect. However, the dietary therapy using sake lees for CKD patients has not been studied. Before examining the effectiveness of sake lees intake in CKD patients, the effect of sake lees on the uremic toxin levels or gut microbiome needs to be explored. Additionally, the changes in D-alanine and D-serine levels in the body should be confirmed.

Our study protocol was approved by the Clinical Trial Review Board of Kanazawa University Hospital on October 27, 2022 (2022-001 [6139]) and available to the public on the website of the Japan Registry of Clinical Trials on November 22, 2022 (jRCT1040220095). We enrolled the first patient on December 21, 2022. By the end of August 2023, we enrolled 19 patients and further recruitment is still ongoing. This pilot study will end in March 2024. Based on the results obtained from this pilot study, a study design will be developed for a future randomized controlled trial to examine the renoprotective effects of sake lees.

## Conclusion

This pilot study provides insight into the development of a new diet focused on gut microbiome and D-amino acids in patients with CKD. Based on the results of our pilot study, a study design will be developed for a future randomized controlled trial to examine the renoprotective effects of sake lees intake.
